#### Baseline patient and scar characteristics

Patients’ baseline characteristics will be extracted from patients’ medical records and consist of the following: age; sex; skin type (Fitzpatrick); scar characteristics, e.g., scar age, cause of the scar; and prior surgery of the selected scar other than fat grafting (exclusion criterion), e.g., split skin grafting.

### Sample size calculation

The primary outcome is the difference in pliability measured by the Cutometer (parameter Ue) between pre- and 12 months post-tSVF-enriched fat grafting. The expected effect size is based on the results of the study by Jaspers et al. on the Coleman fat grafting technique [30]. In this study, scar pliability improved by 22.5%. The mean pliability measure was 0.51. At least this effect is expected to be found in tSVF-enriched fat grafting as well. An additional positive effect of 20% of tSVF-enriched fat grafting (compared to the Coleman technique) is considered a clinically relevant improvement of treatment in this study. Therefore, a sample size calculation was made with an expected effect size of 0.45. With a required minimum of 80% power, a two-tailed test, and *p* < 0.05 considered statistically significant, the required sample size is 41 patients (G*Power 3 version 3.1.9.2). With an anticipated maximum dropout rate of 10% at 12 months, we will need to include 46 patients to compensate for dropout.

### Statistical analysis

Comparisons will be made for all primary and secondary outcome metrics of the selected scar and adjacent normal skin across all follow-up moments, thus pre-, 3, and 12 months post-tSVF-enriched grafting, according to the established data collection protocol [30]. Analyses will be performed using SPSS Statistics, version 27.0 (IBM Corp., Armonk, NY), and Image J (NIH, Behesda, ML) for histological examination of skin biopsies. If data is normally distributed, results will be presented as mean with standard deviation and the primary outcome will be analyses with the paired *T*-test. Furthermore, the repeated measures ANOVA will be performed to detect any overall differences between related means across all time points. If the repeated measures ANOVA is statistically significant, we will run appropriate post hoc tests to highlight exactly where differences occur. If data is not normally distributed, appropriate non-parametric analyses are performed. Data will be analyzed using SPSS, and for histological analysis, GraphPad Prism (version 8.4; GraphPad Software, Inc., La Jolla, USA) will be used. *p*-values < 0.05 will be considered statistically significant.

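### The primary paired t-test and the added repeated-measures ANOVA are complete-case although up to 10% dropout is planned; enrolling 46 restores power but does not correct response-related loss

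*Protocol article*

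**What the plan says.** The Sample size calculation section of the protocol article defines the endpoint: "The primary outcome is the difference in pliability measured by the Cutometer (parameter Ue) between pre- and 12 months post-tSVF-enriched fat grafting". It states that "a sample size calculation was made with an expected effect size of 0.45" and that "the required sample size is 41 patients". It then adds an allowance for loss: "With an anticipated maximum dropout rate of 10% at 12 months, we will need to include 46 patients to compensate for dropout".

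The Statistical analysis section assigns a paired t-test to the primary outcome when data are normally distributed. As a further analysis over baseline, 3 and 12 months, "the repeated measures ANOVA will be performed to detect any overall differences between related means across all time points", with post hoc tests only if the overall test is significant. Non-normal data go to non-parametric methods, which the article does not name.

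The Scar mechanics section schedules pliability at 3 months as well. Table 1 excludes patients who will not commit to attending every follow-up visit.

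**The concern.** Both named tests work on complete records. A patient lost after month 3 has a baseline and a 3-month pliability value, yet contributes nothing to the primary test. Raising enrolment from 41 to 46 replaces the number of lost patients. It does not make the remaining ones representative.

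The design makes this matter more than usual. The trial is a single-arm before-after study, so selective loss enters the estimated change directly, with no control arm in which a similar loss could cancel it. The Discussion also intends comparison with cohorts treated by other fat grafting techniques. Differences in who drops out would pass straight into that comparison.

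**Working it through.** **1. The plan's own figures.** Inputs from the Sample size calculation: effect size 0.45 (read as mean change divided by the SD of the change), two-sided 5% level, 80% power. The power of a paired t-test comes from the noncentral t distribution with n − 1 degrees of freedom and noncentrality 0.45·√n.

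- n = 40: power 0.793. n = 41: power 0.803. So 41 is reproduced.
- 41 / (1 − 0.10) = 45.6, rounded up to 46. So 46 is reproduced.
- If all 46 were complete, power would be 0.848.

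The inflation therefore does what it is meant to do for precision.

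**2. Who each analysis uses.**

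| Patient has | Paired t-test | Repeated-measures ANOVA | Mixed model |
|---|---|---|---|
| Baseline, 3 and 12 months | used | used | used |
| Baseline and 12 months only | used | dropped | used |
| Baseline and 3 months only | dropped | dropped | used |
| Baseline only | dropped | dropped | used, but adds little |

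**3. Direct arithmetic at the planned loss.** 46 − 41 = 5 patients missing, and 5/46 = 10.9%. Suppose the 41 completers average 0.45 SD.

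- Leavers would have averaged 0: (41 × 0.45 + 5 × 0)/46 = 0.401, so the completers overstate by 0.05.
- Leavers would have averaged −0.45: (41 × 0.45 − 5 × 0.45)/46 = 0.352, an overstatement of 0.10.
- Leavers would have averaged 0.90: (41 × 0.45 + 5 × 0.90)/46 = 0.499, an understatement of 0.05.
- As a ceiling, if exactly the worst 5 of 46 leave, the bias is φ(z)/(1 − p) with p = 5/46, which is about +0.21 SD.

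**4. Simulation.** The document gives no SD of change, visit correlation or dropout mechanism, so these are assumptions:

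- SD of the change 1, and true mean change 0.45 at both visits.
- Equal correlation of 0.3, 0.5 or 0.7 between visits.
- Logistic dropout with slope 1 or 2 per SD of change (worse responders more likely to leave), tuned to 10.9% missing at 12 months.
- 6,000 trials of 46 patients per setting.

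The mixed-model estimate is the likelihood estimate using baseline and month 3 where observed. Bias in the 12-month change, in SD:

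| Dropout depends on | Complete pairs | Mixed model |
|---|---|---|
| Nothing (random) | 0.00 | 0.00 |
| Observed month-3 change | +0.049 to +0.078 | −0.001 to +0.003 |
| Unseen 12-month change | +0.099 to +0.155 | +0.063 to +0.113 |
| Unseen 12-month change, leaving before month 3 | +0.096 to +0.153 | +0.068 to +0.133 |

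In the third row the model removes between 1 − 0.113/0.153 = 26% and 1 − 0.063/0.099 = 36% of the bias. In the fourth row it removes between 13% and 32%.

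The spread of the two estimators is practically the same. In the month-3-driven settings it is 0.151 to 0.155 for complete pairs and 0.153 to 0.156 for the model.

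**The case against.** **A paired t-test on change is a valid analysis of a before-after endpoint, and it matches the sample size.** This stands. The plan contains no error or contradiction here; the point is that a better analysis of data already scheduled is available.

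**Missing-data handling may sit elsewhere.** The article presents itself as a summary of the approved protocol, and neither that protocol nor an analysis plan is at hand. The absence of a missing-data rule is therefore not the finding. The finding rests on the tests that the article names. A later document could add sensitivity analyses, but the primary test as fixed here would remain complete-case.

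**The effect is modest.** This also stands. With 41 pairs the standard error is about 1/√41 = 0.156 SD, so a bias of 0.05 to 0.08 is roughly a third to a half of a standard error. A confidence interval does not show it, however. The sample size section treats an additional 20% over the Coleman technique as clinically relevant. How 0.45 was derived from this is not shown. If the 20% is relative and already included, the increment is 0.45 − 0.45/1.2 = 0.075 SD, about the size of the bias. If it is absolute (22.5% to 42.5%), the increment is 0.45 × 20/42.5 = 0.21 SD and the bias is a smaller share.

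**Four stronger readings go beyond the documents.**

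- A reader might infer that poor responders will leave and the result will be inflated. Nothing in the article says who drops out, and the commitment required by Table 1 should lower the risk, although 10% is still planned for.
- A reader might infer that a mixed model on all 46 removes the problem. It does so only if dropout depends on observed values.
- A reader might infer that the primary test needs all three visits. It needs only baseline and 12 months; the three-visit requirement belongs to the ANOVA, which is an additional analysis.
- A reader might work with 20% dropout, or with further loss at month 3. The article gives neither figure; it states at most 10% at 12 months.

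**Conclusion.** The point holds in a limited form. As named, the primary test discards patients without a 12-month value, the additional ANOVA discards anyone with an incomplete set of visits, and the enlarged enrolment protects power only.

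Whether this biases the result depends on the dropout mechanism, which the article neither states nor excludes. At the planned loss the bias is:

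- zero under random dropout;
- about +0.05 to +0.08 SD against 0.45 if dropout follows a poor month-3 response;
- about +0.10 to +0.16 SD if it follows a poor, unseen 12-month response;
- downward if good responders leave.

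These sizes rest on the assumed correlations and dropout slopes above. The change is worth making because it uses data already scheduled and costs practically no precision. It does not show that the planned estimate will be wrong.

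**What to change.** Replace the repeated-measures ANOVA with a linear mixed model that has visit as a three-level factor (baseline, 3 and 12 months) and an unstructured covariance, fitted to all patients with a baseline value. Take the 12-month minus baseline contrast with its 95% CI as the primary estimate. The overall test of visit from the same model serves the purpose of the ANOVA. Keep the completers' paired t-test as a sensitivity analysis.

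Because the model is valid only under missing at random and only reduces bias otherwise, add one simple missing-not-at-random analysis, for example delta-adjusted imputation for dropouts. Its effect is easy to read: with 5 of 46 imputed, lowering the imputed values by δ lowers the estimate by 5/46 × δ = 0.109 δ, so δ = 0.45 SD moves it by 0.05.

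The cost is analysis wording. No patients, visits or measurements are added, the sample size of 46 stays, and the model can be fitted in the SPSS version already named. The remaining limit is that patients who leave before month 3 contribute only a baseline value, so the model can recover little for them.

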## Discussion

The aim of this non-randomized intra-patient before-after early phase trial is to assess the efficacy of tSVF-enriched fat grafting on the pliability of adherent scars caused after burn injury or fasciitis necroticans or degloving injury. The potential therapeutic capability of tSVF in adherent scars will be measured by validated objective and subjective scar assessment tools.

This proposed non-randomized study design is part of a larger series of consecutive non-randomized trials with identical study design and standardized algorithm and outcome assessment scheme to allow for identical scar follow-up [30]. The only difference between these studies is the fat grafting technique. These series of studies aim to determine the optimal (fat grafting) treatment for patients with adherent scars. Through the same study design, core outcome set, and patient populations (same inclusion criteria), the efficacy of the various techniques can be systematically compared. Moreover, it will enable historical cohort comparison over time. In this type of cohort series, as compared to classical randomized controlled trials (RCTs), no limiting inclusion criteria are used which provides a better representation of the true patient population to our opinion (real-world evidence). This is in contrast to RCTs in which study populations often only present a small part of the true population due to strict inclusion and exclusion criteria (e.g., exclusion of comorbidities). However, a limiting factor of this study is the lack of a direct comparison of two or more fat grafting techniques under the exact same circumstances as is the case in a RCT. Nonetheless, the real-world data setting that this study provides may result in evidence of the efficacy of tSVF-enriched fat grafting in scar treatment.

In this study, the chosen primary outcome parameter is scar pliability measured by the Cutometer. This scar pliability assessment is a reliable, non-invasive, and painless parameter to assess the therapeutic effects of fat grafting as scar remodeling treatment and the Cutometer is also one of the most researched validated measurement devices to assess tissue pliability and elasticity [39]. Apart from the assessment of objective scar tissue features, inclusion of subjective patient measurements in scar assessment is essential. Subjective scar features are assessed using the validated and world-wide used POSAS questionnaires [26]. Besides the standardized protocol and core outcome set, the power of our trial design is also the proposed combination of clinical and histological analysis of tSVF-treated scar samples. Together, they offer great potential to measure therapeutic efficacy in a real-world setting. This combination will also provide insight in the underlying mechanism of potential regenerative effects of tSVF on scar tissue, which may have direct implications for future research and clinical applications. Moreover, the long follow-up period will reassure that fat, and possibly also tSVF, has initiated regenerative processes and scars have had allowance to reverse to healthier dermal tissue so that this can be objectified with the data outcome set [40].

To ensure equal quality of treatment in the participating centers of this multicenter study and to minimize the effect of confounding factors, several standardization measures were applied. For example, specific durations have been set for procedural steps, e.g., 80 min for normal fat grafting procedures and 20 min for concentrating and injection of SVF-enriched fat grafts. Furthermore, all fat grafting procedures will be carried out according to the Coleman technique and centers will use the same fractionators to manufacture tSVF. Moreover, only plastic surgeons with significant experience with fat grafting procedures will perform the surgeries to ensure equal standard of care. Finally, uniform outcome measures were selected and measurements will be executed by the same trained observers on all follow-up moments (not plastic surgeons to prevent observer or confirmation bias). Patients of the participating Dutch Burn Centers possibly provide an accurate model for burn patients and patients with adherent scars in most high-income countries and the surgical procedure is easily replicable in other like clinical environments where fat grafting can be carried out. This may improve the generalizability of the studies’ conclusions. We believe that our non-randomized multicenter study design is sufficiently powerful to provide such potential evidence that may alter the standard of care. This has precedent, for instance in the non-randomized trial of Jaspers et al., after which fat grafting for adherent scars became insured healthcare in the Netherlands.

In summary, our non-randomized trial will contribute to further optimizing fat grafting treatments of patients with adherent scars and may potentially lead to better and more optimal treatment options for adherent scars than other fat grafting techniques.

## Trial status

This study design is a summary with backgrounds and explanations of the CCMO-approved protocol (version 2.0, 27 August 2020 NL72094.000.20) and complies with the guideline of Good Clinical Practice (GCP). Inclusion opens at December 2021 and is expected to be completed in October 2024.

## Data Availability

Not applicable.

## Abbreviations

ASC: Adipose-derived stromal cell
CCMO: National Dutch Ethical Committee
cSVF: Cellular stromal vascular fraction
FAT: Fractionation of adipose tissue
MSS: Manchester Scar Scale
POSAS: Patient and Observer Scar Assessment Scale
SVF: Stromal vascular fraction
tSVF: Tissue stromal vascular fraction
VSS: Vancouver Scar Scale
